#### Screening: inclusion visit

Eligible patients will be identified either during the cancer diagnosis disclosure consultation with the surgeon or during the consultation with an Advanced Practice Nurse (APN) as part of the pre-therapeutic care pathway in the gynaecological surgery. They will provide written informed consent after receiving comprehensive information about the study and being given adequate time to consider their participation.

#### Initial assessment/randomisation (T0)

A clinical and paraclinical examination by the multidisciplinary sports medicine team during a day care hospital visit, before any therapeutic intervention, will include clinical data, cardiopulmonary exercise testing, pulmonary function testing, 24-hour Holter ECG monitoring, additional examinations and Self-Report Questionnaires. Patients will also be instructed on daily PA self-monitoring via an electronic or paper logbook. The estimated completion time is 2 min per day.

They will be randomised into two groups.

#### Follow-up visit at the initiation of AI (T1)

At the start of AI therapy, all patients will undergo a clinical evaluation, functional tests, adverse event monitoring and Self-Report Questionnaires. This visit will occur in the sports medicine department and be conducted by a sports medicine physician.

For the control group, the personalised APA programme will start at this stage.

#### Follow-up visit at the end of the 12-week personalised APA programme (T_APA_)

T_APA_ will include evaluations similar to those performed at T1.

#### End-of-study visit (T2)

The end of the study will be defined as 6 months after the initiation of AI therapy, which corresponds to the median time point at which both the peak of AIMSS symptoms and treatment discontinuation due to AIMSS are reported in the literature.^19^ This assessment will follow the same procedure as T1 and T_APA_, with the addition of cardiopulmonary exercise testing and 24-hour Holter ECG monitoring.

Semi-structured individual interviews will be conducted by two researchers with patients and healthcare professionals.

### Sample size

#### Sample size for the primary outcome

The expected prevalence of AIMSS in the standard care group is approximately 40%. We hypothesise a 50% reduction (20%) in the experimental group with early implementation of APA.^20^ Considering an alpha risk of 5%, a power of 80% and a two-sided hypothesis, 82 patients per arm will be required. Assuming 10% unusable data, a total of 182 patients will be included.

Sample size for the qualitative component of the mixed-methods study (secondary implementation aim).

The principle of theoretical saturation will guide the sample sizes of the two groups (patients and healthcare professionals), once the collected data are sufficient to explain the phenomenon. Data collection, conducted progressively and in parallel with analysis, will define the final sample size.^21^

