### Study objectives

The primary study aim is to compare the prevalence of musculoskeletal pain after 6 months of AI therapy between patients who started a personalised APA programme at the start of their care pathway and those receiving usual care.

The secondary objective is to explore contextual factors influencing the implementation of the APA programme in real-world oncology care, including perceived barriers and facilitators, based on quantitative and qualitative data collected from both patients and healthcare professionals.

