### Outcomes

#### Primary outcome

The primary outcome will be the score for the most intense musculoskeletal pain, assessed with the Nordic-style questionnaire, 6 months after the introduction of the AI (T2).

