.AIMSS, aromatase inhibitor-induced musculoskeletal symptoms; APA, adapted physical activity ; APN, Advanced Practice Nurse; BMI, body mass index; CG, control group; CRP, C-reactive protein; D, day; DLCO, diffusing capacity of the lung for carbon monoxide; EG, experimental group; FEV1, forced expiratory volume in 1 s; HOMA-IR, Homeostatic Model Assessment for Insulin Resistance; IV, inclusion visit; M, month; MWT, 6-minute walk test; PA, physical activity; PEF, peak expiratory flow; RV, residual volume; T0, pre-therapeutic phase; T1, initiation of the aromatase inhibitors; T2, 6 months after the initiation of the aromatase inhibitors; T_APA_, end of the 12-week APA programme; TLC, total lung capacity; VC, vital capacity; VO₂ max, maximal oxygen consumption; VO₂ peak, peak oxygen consumption; VT, tidal volume.

**Table 2 T2:** Summary of secondary outcomes and data collection methods for the effectiveness aim

Outcome domain	Outcome measure	Data collection	Assessment modality
**Global pain***	Musculoskeletal pain	Musculoskeletal pain intensity and localisation	Nordic-style questionnaire†
	Overall pain	Self-rated overall pain	Numerical Rating Scale†
	Quality of life	Quality of life score	FACT-B†, FACT-ES†
	Fatigue	Fatigue score	FACIT – Fatigue†
	Anxiety	Anxiety and depression scores	HADS†
**Cognitive function**		Perceived cognitive impairments	FACT-Cog†
**Physical condition**	Respiratory function	FEV1, PEF, VT, VC, RV, TLC, DLCO	Pulmonary function tests
	Cardiac function	VO₂ peak, VO₂ max, maximal heart rate, VO₂ at VT1, cardiac output at VT1, heart rate at VT1, blood pressure, oxygen saturation	Cardiopulmonary exercise test
	Cardiorespiratory endurance	Distance walked in 6 minutes	6-minute walk test
	Muscular strength	Isometric grip strength	Handgrip strength test
	PA level	Habitual levels of PA	Marshall questionnaire†, IPAQ†
**Body composition**	Anthropometric measurements	Body weight, height, body mass index, waist circumference and 4-site skinfold	Anthropometric assessment
	Malnutrition	MUST score	MUST†
**Evolution of a metabolic syndrome**		Waist circumference	Anthropometric assessment
		Blood pressure	Blood pressure measurement
		Lipid profile, assessment of insulin resistance and inflammatory status	Blood tests: lipid profile, HOMA-IR, C-reactive protein
**HRV‡**		HRV parameters	24-hour Holter ECG recording
**Therapeutic adherence to the AI**		Therapeutic adherence to the AI	Girerd self-assessment questionnaire†

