#### Primary data collection

The prevalence of musculoskeletal pain will be assessed using the Nordic-style questionnaire, a validated tool for detecting musculoskeletal disorders. It consists of closed-ended questions and can be used as a self-reported questionnaire.

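### The 80% power is stated for AIMSS prevalence (40% vs 20%), but the planned primary endpoint is the worst musculoskeletal pain score at T2 from any cause, with no use of the T0 pain data

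*Protocol article*

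**What the plan says.** The protocol article describes the primary quantity in several ways.

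- **Study objectives:** "The primary study aim is to compare the prevalence of musculoskeletal pain after 6 months of AI therapy".
- **Primary outcome:** "The primary outcome will be the score for the most intense musculoskeletal pain, assessed with the Nordic-style questionnaire", taken at T2. Under Quantitative data analysis, this maximum intensity is compared between groups by a t-test or a Wilcoxon-Mann-Whitney test.
- **Primary data collection:** "The prevalence of musculoskeletal pain will be assessed using the Nordic-style questionnaire".
- **Sample size for the primary outcome:** "The expected prevalence of AIMSS in the standard care group is approximately 40"%. Then: "We hypothesise a 50% reduction (20%) in the experimental group with early implementation of APA". Then: "Considering an alpha risk of 5%, a power of 80% and a two-sided hypothesis, 82 patients per arm will be required". Finally: "Assuming 10% unusable data, a total of 182 patients will be included".

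Three further places bear on the point. The Background presents AIMSS as a syndrome caused by aromatase inhibitors (AI). The patient eligibility criteria admit women up to age 75, and the only musculoskeletal exclusion is a condition that rules out cycling. Table 1 schedules the self-report questionnaires at T0, T1, T_APA and T2, and Table 2 shows that the Nordic-style questionnaire is one of them and records "Musculoskeletal pain intensity and localisation".

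**The concern.** AIMSS is pain attributed to the AI. The worst musculoskeletal pain at T2 also takes in pain that predates randomisation and pain from surgery, chemotherapy or radiotherapy between T0 and T1. Nothing in the article limits the primary outcome to new, worsened or AI-related pain, and the stated primary test compares the arms at T2 without reference to T0.

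Two things are at stake. First, the stated power belongs to a quantity that the primary analysis does not test. It is a proportion where the test uses a score, and AI-related pain where the test uses pain of any origin. Second, if background pain is common and the programme does not change it, it raises both arms and narrows the gap between them. The T0 measurement that could remove much of this noise is already collected from every woman but left out of the primary comparison.

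**Working it through.** **Inputs from the sample size section.** Control 0.40, experimental 0.20, two-sided alpha 0.05, power 0.80, 82 per arm.

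**1. Reproduce the stated figure.** Two-proportion formula with pooled variance and no continuity correction:

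n = [1.96·√(2·p̄(1−p̄)) + 0.8416·√(p1(1−p1) + p2(1−p2))]² / (p1−p2)²

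With p̄ = 0.30: [1.96·√0.42 + 0.8416·√0.40]² / 0.04 = [1.270 + 0.532]² / 0.04 ≈ 81.2, so 82 per arm. Power at 82 per arm is 80.4%. The arithmetic is right for a comparison of 40% with 20%. Allowing for 10% loss by division gives 82/0.9 = 91.1, or 92 per arm and 184 in total; the stated 182 is two short, which is immaterial.

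**2. Add background pain (assumption).** Let a share b of women have musculoskeletal pain at T2 that is not AIMSS, equal in both arms, independent of AIMSS and unaffected by the programme. The prevalence of any pain is then p = b + (1−b) × AIMSS rate. The article gives no value for b, so a range is shown.

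Power = Φ[(d − 1.96·SE0)/SE1], where d = p1−p2, SE0 = √(2p̄(1−p̄)/82) and SE1 = √((p1(1−p1)+p2(1−p2))/82).

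Example, b = 10%: p1 = 0.10 + 0.90×0.40 = 0.46 and p2 = 0.10 + 0.90×0.20 = 0.28. SE0 = 0.0754, SE1 = 0.0741, and (0.18 − 0.1478)/0.0741 = 0.435, so power is 66.8%.

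| Background b | Any pain, control vs experimental | Power at 82 per arm | n per arm for 80% |
|---|---|---|---|
| 0% | 40% vs 20% | 80.4% | 82 |
| 5% | 43% vs 24% | 73.6% | 96 |
| 10% | 46% vs 28% | 66.8% | 112 |
| 20% | 52% vs 36% | 54.2% | 150 |
| 30% | 58% vs 44% | 43.3% | 199 |

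**3. Relax the assumption that the programme leaves background pain alone.** Suppose the programme halves b in the experimental arm. At b = 10%, p2 = 0.05 + 0.95×0.20 = 0.24; 46% vs 24% has 84.6% power. At b = 20%, p2 = 0.10 + 0.90×0.20 = 0.28; 52% vs 28% has 88.8% power. The loss disappears.

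**4. Suppose 40% already means all pain.** If only the AI-related part is halved, a 5% background inside the 40% gives an AIMSS rate of (0.40−0.05)/0.95 = 0.368 and p2 = 0.05 + 0.95×0.184 = 0.225, with power 67.9%. A 10% background gives p2 = 0.25 and power 53.7%. If all pain is halved, 40% vs 20% and about 80% stand for a prevalence.

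**5. Does the dilution carry over to a score?** A simulated 0–10 worst-pain score was tested by Wilcoxon at 82 per arm. Intensities were assumed uniform from 1 to 10 when pain is present, and the observed score was the larger of AI-related and background pain. Power was about 79% with no background, and roughly 65%, 50% and 40% at 10%, 20% and 30%. This is illustrative only, because the article gives no score distribution or standard deviation.

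**The case against.** The strongest reply has five parts.

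- **The two-proportion powers are not for the planned test.** This stands. The primary outcome is a score with no cut-off, so it would be wrong to say that the endpoint counts T0 pain as an event. The figures in steps 2 to 4 apply only if a prevalence is kept. The reply also supports the main point: the stated 80% has the same limitation.
- **The 40% may already be the prevalence of all pain.** This is possible. The article's key-points box uses AIMSS as shorthand for musculoskeletal pain, and the source of the 40% cannot be consulted here. A reader might infer that 40% vs 20% cannot be the contrast in the measured endpoint; the documents do not establish that.
- **The programme may reduce background pain.** This is also possible. It starts at T0 in the experimental arm, and the article's rationale is that early activity could ease treatment-related symptoms generally. Step 3 shows that a halving removes the loss.
- **Randomisation balances earlier pain in expectation.** This is correct. A difference at T2 can be attributed to the timing of the programme, so the comparison is not invalid. What remains uncertain is whether the difference concerns AIMSS in particular.
- **T0 data are used elsewhere, and covariates may be left to a fuller document.** Comparisons of change are planned for secondary outcomes, and an unspecified covariate alone would not be a finding. But the article does state its primary outcome and test, and sizes the trial on something else.

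**Conclusion.** The stated 80% power does not describe the planned primary endpoint. It is calculated correctly for AIMSS prevalence of 40% vs 20%, while the outcome and test use a worst-pain score from any cause, women with existing pain can enter, and T0 pain plays no part in the primary comparison. This follows from the text alone.

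The size of any shortfall is conditional. With background pain independent of AIMSS and untouched by the programme, a prevalence comparison at 82 per arm would have about 74%, 67%, 54% and 43% power at 5%, 10%, 20% and 30% background. With background pain halved as well, nothing is lost.

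A reader might infer that the trial is definitely well below 80% power. The documents do not support that: they give neither a background rate nor any statement that the programme leaves such pain unchanged. Nor do they show that the logistic model for AIMSS risk factors misclassifies earlier pain, since the article does not say that this model takes any T2 pain as a case.

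**What to change.** State one primary outcome, in the same terms in the objective, outcome, sample size and analysis sections, and use each woman's T0 Nordic-style pain data in it. There are two acceptable routes:

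1. Keep the T2 worst-pain score and adjust it for the T0 score.
2. If a prevalence is kept, define the event as pain that is new, or worse by a pre-set margin, since T0.

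Then restate the power for that same quantity, giving its rates or standard deviation and the assumption made about background pain. Use the same case definition in the AIMSS risk-factor model. Report the prevalence of any pain as secondary. A version referenced to T1 should be supportive only, because T1 comes after the programme has started in the experimental arm.

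The cost is small: one covariate or derived variable, and no extra visit, because the T0 questionnaire is already scheduled. The restated power may be less favourable. Pain that is new since T0 still includes pain from surgery, chemotherapy or radiotherapy, so it should not be labelled AIMSS without qualification.

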### Recruitment

#### Recruitment for quantitative outcomes

The estimated pool of eligible patients is 240 patients at the gynaecological surgery departments at the Saint-Etienne University Hospital and 360 at the gynaecological surgery departments at the Lyon University Hospital over the full 24-month inclusion period. The APIS study will recruit 72 women at the Saint-Etienne Hospital and 110 women at the Lyon Hospital, for a total of 182 subjects.

#### Recruitment for the qualitative component

A purposive sampling strategy based on the maximum variation method will be used to ensure a diverse representation of real-life clinical situations.^22^ This approach will be designed to capture a wide range of perspectives and to identify shared patterns across heterogeneous experiences.

The patient sample will include individuals from both the experimental and control groups, enabling a comprehensive understanding of the intervention’s implementation across varying contexts.

### Data collection

All functional tests and measurements will be performed as part of routine care in a sports medicine department by professionals trained to ensure the reliability, reproducibility and standardisation of the assessments.

#### Primary data collection

The prevalence of musculoskeletal pain will be assessed using the Nordic-style questionnaire, a validated tool for detecting musculoskeletal disorders. It consists of closed-ended questions and can be used as a self-reported questionnaire.

#### Secondary data collection: effectiveness aim

Table 2 presents the outcome domains, specific measures and data collection modalities for the secondary outcomes evaluated as part of the hybrid type 1 trial’s effectiveness aim.

Validated questionnaires and functional tests were selected based on their relevance and prior use in oncology and exercise studies. Full references are available in the online supplemental file 2.

### Secondary data collection: implementation aim

Quantitative data will be collected through questionnaires and will include indicators such as participation rates, programme adherence, patient satisfaction and the representativeness of both patients and healthcare professionals relative to the target population.

The qualitative analysis will be conducted through semi-structured interviews using the Theoretical Domains Framework (TDF) and COM-B Model (Capability, Opportunity, Motivation – Behaviour).^23^ The TDF will help identify and describe barriers and facilitators to APA programme implementation from the perspective of patients and healthcare professionals.^24^

Table 3 summarises the corresponding indicators and data sources for each RE-AIM component.

**Table 3 T3:** RE-AIM framework: definitions and data collection methods in the APIS study

RE-AIM dimension	Definition	Data collection
Reach	Proportion and representativeness of individuals in the target population who participated in the intervention	Percentage of patients who completed all stages of the study, dropout rate at each key stage of the study and reasons for dropout. Comparison of socio-demographic and clinical characteristics of participants (age, treatment, etc) with those of the target population.
Effectiveness	Impact of the intervention on individual outcomes, including benefits, adverse effects and subgroup variability	Primary and secondary outcomes are defined in the effectiveness study.
Adoption	Engagement of individual healthcare professionals in delivering the intervention, in line with the exploratory focus of hybrid type 1 trials	Proportion of healthcare professionals involved in the delivery of the APA programme, by specialty, relative to the total number of eligible professionals at each participating site. Semi-structured interviews with healthcare professionals exploring contextual and behavioural determinants of adoption, such as professional identity, beliefs about capabilities, motivation and perceived organisational barriers or facilitators.
Implementation	Fidelity of intervention	Frequency: Average number of PA sessions performed per week (self-reported and measured within the APA programme). Intensity: Intensity level of PA sessions measured by a perceived exertion scale (Borg scale) and objective data. Time: Average duration of sessions (in minutes). Type: Proportion of sessions complying with the type of exercise recommended by guidelines. Programme-level adaptations (eg, changes in session format, scheduling or delivery methods) will be documented, categorised (structural, organisational or patient-related) and analysed in relation to their impact on ongoing participation. Patient-reported implementation outcomes: motivation* (EMAPS scale) and satisfaction/APA programme (5-point Likert scale). Qualitative data on barriers and facilitators, necessary adaptations and rationale for maintaining or modifying the APA intervention. They will be collected through semi-structured interviews with both patients and healthcare professionals.
Maintenance	Sustainability of the intervention at both the individual and professional levels	Reassessment of FITT indicators at T2. Maintenance will be assessed at T2 to evaluate the sustainability of behaviour and practice changes beyond the APA intervention period. Data on PA levels obtained from logbooks and self-reported questionnaires at T2. Qualitative data on barriers and facilitators to long-term integration of PA into daily life and clinical practice.

* Motivation will be measured using the Échelle de Motivation pour l’Activité Physique à des fins de Santé (EMAPS), a French-language validated tool based on self-determination theory.

APA, adapted physical activity; FITT, Frequency, Intensity, Time, and Type; PA, physical activity.

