### Study design and assessment time

Figure 3 illustrates the study design aligned with the clinical care pathway, including the timing of randomisation, the APA intervention and data collection time points. Data collection will be structured around standardised key events in the treatment pathway: T0 (during the pre-therapeutic phase), T1 (at the initiation of the AI), T_APA_ (at the end of the 12-week personalised APA programme) and T2 (6 months after the initiation of the AI). The assessment times will be defined by the stages of the care pathway, rather than fixed calendar times, to account for variability in treatment protocols. The interval between T0 and T1 may range from 1 month for patients treated with mastectomy alone, to up to 7 months for those treated with surgery, chemotherapy (with or without targeted therapy) and radiotherapy. The interval between T1 and T2 is fixed at 6 months.

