#### Qualitative data management

Two distinct semi-structured interview guides, one for patients and one for healthcare professionals, were developed based on the 14 domains of the TDF, following the methodology proposed by Cane *et al*.^25^ Each domain was explored through open-ended questions, supplemented by follow-up prompts as needed to elicit detailed responses.^24^

The guides were reviewed for content validity by two oncology healthcare professionals and a methodological expert to ensure their appropriateness for the target populations. Pilot testing was conducted with a patient partner and a healthcare professional, resulting in refinements to the clarity and wording of the interview items.

Interviews will be conducted at time point T2 by a doctoral candidate (NP) and a patient-researcher (AG), both of whom are trained in qualitative research methods. Each interview will last approximately 25–35 min and will be conducted in a single videoconferencing session. All participants will receive comprehensive written and verbal information about the study, including its objectives, interview procedures and data management protocols. With informed consent, interviews will be audio-recorded using a digital device, securely transferred to a password-protected computer and subsequently deleted from the recording device. Each interview will be transcribed verbatim and pseudonymised. NVivo V.15 software (QSR International) will be used to organise and analyse the data.

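### Table 3 dates professional-level Maintenance at T2, a per-patient date at which the sites are usually still delivering trial APA, so the data can show anticipated sustainability but not maintained practice

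*Protocol article*

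**What the plan says.** Table 3 (Secondary data collection: implementation aim) defines Maintenance as "Sustainability of the intervention at both the individual and professional levels". It then dates it: "Maintenance will be assessed at T2 to evaluate the sustainability of behaviour and practice changes beyond the APA intervention period". The other data sources in that row are patient measures (FITT indicators, logbooks, questionnaires). The one item that touches professionals is "Qualitative data on barriers and facilitators to long-term integration of PA into daily life and clinical practice".

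T2 belongs to the patient. Study design and assessment time says: "The assessment times will be defined by the stages of the care pathway, rather than fixed calendar times". End-of-study visit (T2) says: "The end of the study will be defined as 6 months after the initiation of AI therapy". The same section places the interviews with patients and with professionals at that visit, and Qualitative data management repeats it: "Interviews will be conducted at time point T2". The eligibility criteria for healthcare professionals concern role, caseload and consent, and give no index date.

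Three further statements set the calendar:
- Recruitment for quantitative outcomes gives the pool of eligible patients "over the full 24-month inclusion period".
- Follow-up visit at the initiation of AI (T1) starts the control group's programme at T1.
- Intervention describes a first supervised programme of 12 weeks, then renewal or adjustment phases that may run to the end of the trial.

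**The concern.** Maintenance at professional level asks whether practice persists once the intervention has stopped. That needs a time point after delivery has stopped for the professional. T2 is a different date for each woman, and entry is staggered over two years. When one woman reaches T2, the same staff will usually be running the programme for others. What they say then describes practice under the trial, or their expectations of what will follow.

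The text is also inconsistent for a single patient. If renewal can run to the end of the trial and the study ends at T2, then T2 closes the intervention period and does not lie after it.

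What is at stake is the wording of one implementation conclusion. Implementation is the stated secondary objective, and all five RE-AIM dimensions are to be examined. A statement that practice changes were sustained after the intervention would not be supported by data gathered in this way.

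**Working it through.** **Inputs from the protocol article.** Inclusion 24 months; T0–T1 gap 1 to 7 months; T1–T2 fixed at 6 months; first APA programme 12 weeks = 84/30.4375 = 2.76 months; experimental APA starts at T0, control APA at T1.

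**Range of T2 dates (months from the start of inclusion).** Earliest: 0 + 1 + 6 = 7. Latest: 24 + 7 + 6 = 37.

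**When the last first 12-week block could end, for a woman randomised at month 24.**
- Experimental arm: 24 + 2.76 = 26.76.
- Control arm, T0–T1 gap of 1, 4 or 7 months: 24 + 1 + 2.76 = 27.76; 24 + 4 + 2.76 = 30.76; 24 + 7 + 2.76 = 33.76.

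**Share of T2 dates before each cut-off c.** The article gives no accrual pattern. Assume randomisation uniform over 0–24 months and, independently, the gap uniform over 1–7 months (mean 4). For c between 13 and 31 the share is (c − 6 − 4)/24. For c between 31 and 37 it is 1 − (37 − c)²/(2 × 24 × 6).
- Close of recruitment, c = 24: 14/24 = 58%.
- Experimental first blocks only, c = 26.76: 16.76/24 = 70%.
- Last control with a 1-month gap, c = 27.76: 17.76/24 = 74%.
- Last control with a 4-month gap, c = 30.76: 20.76/24 = 86.5%.
- Last control with a 7-month gap, c = 33.76: 1 − 3.24²/288 = 96%.

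**A second measure.** A simulation of 182 women, both sites pooled, with uniform accrual and alternating arms, counted the T2 dates at which at least one other woman was in her first 12-week block. The share was 85% with a constant gap and 92% with gaps spread over 1 to 7 months. If every programme were renewed up to the woman's own T2, 181 of 182 T2 dates (99.5%) would overlap with someone else's APA, and the last T2 would coincide with the end of delivery.

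**Contrast with the individual level.** From the end of a woman's first block to her T2 is 6 − 2.76 = 3.24 months for a control. For the experimental arm it is 1 + 6 − 2.76 = 4.24 to 7 + 6 − 2.76 = 10.24 months. If her programme is not renewed, some individual-level maintenance can be seen at T2. Professionals have no corresponding interval.

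**The case against.** Several points on the other side have force.

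- **No practice measure is planned for professionals.** A reader might infer that the trial will report an inflated rate of maintained practice, or that it can learn nothing about sustainability. The text supports neither. The professional part of the row is qualitative, so there is no rate or count to inflate, and staff can describe barriers to long-term integration while delivery is running. What stands is a claim wider than its data.
- **The shares describe patient T2 dates.** The interviews are a purposive sample, collected progressively until saturation (Sample size; Recruitment for the qualitative component). Nothing ties them in proportion to patient T2 dates, so no percentage above is a share of professional interviews.
- **The 96% uses the latest possible cut-off.** It needs the last woman randomised to be a control with the longest gap. Study design also says that the control timing reflects current local practice, so control-arm APA is arguably routine care. Counting only experimental first blocks gives 70%: overlap is still usual, but about 30% of T2 dates fall later.
- **Scale-up.** A reader might infer that professional Maintenance feeds the later phase. Limitations makes that phase conditional on positive findings and does not name Maintenance as an input.
- **Condensation.** An article may leave the date of each professional's interview to the full protocol, and an end-of-study intention is possible. But this article states both a time point and what that time point will show, and the two do not fit.

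**Conclusion.** The point holds as a limit on interpretation. Table 3 claims to assess practice changes after the intervention period at a date defined per patient. On the article's own intervals, trial APA is usually still running at the sites on that date. Between about 70% and 96% of patient T2 dates precede the end of the last first block. The figure depends on which blocks count and rests on assumed uniform accrual and gaps; renewals would raise it. That T2 dates overlap with continuing delivery follows from staggered entry and does not rest on the exact percentages.

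The professional interviews can therefore support statements about perceived or anticipated sustainability, not about maintained practice. This is a minor point on a secondary, exploratory outcome. The primary comparison and the sample size do not depend on it.

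**What to change.** 1. Reconcile three passages: Intervention (renewal up to the end of the trial), End-of-study visit (T2 as the end of the study) and the Maintenance row of Table 3 (T2 as later than the intervention period). Which of them changes is for the sponsor to decide.

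2. In the Maintenance row, delete *and practice changes* and the reference to the professional level. Report the professional interviews under Implementation or as anticipated sustainability. This is a wording change with no added data collection.

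3. If professional-level Maintenance is to be kept, leave the progressive interviews in place for Adoption and Implementation. Take the professional Maintenance questions only from interviews held after APA delivery to participants has ended at that site. The cost is later contact and the loss of some staff who have moved on. Moving every professional interview to that date is not advised: it would conflict with progressive collection to saturation and would place the Adoption and Implementation questions further from the events they concern.
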